## Abstract

**Background:**

Double-layer compared to single-layer closure of the uterus after a caesarean section (CS) leads to a thicker myometrial layer at the site of the CS scar, also called residual myometrium thickness (RMT). It possibly decreases the development of a niche, which is an interruption of the myometrium at the site of the uterine scar. Thin RMT and a niche are associated with gynaecological symptoms, obstetric complications in a subsequent pregnancy and delivery and possibly with subfertility.

**Methods:**

Women undergoing a first CS regardless of the gestational age will be asked to participate in this multicentre, double blinded randomised controlled trial (RCT). They will be randomised to single-layer closure or double-layer closure of the uterine incision. Single-layer closure (control group) is performed with a continuous running, unlocked suture, with or without endometrial saving technique. Double-layer closure (intervention group) is performed with the first layer in a continuous unlocked suture including the endometrial layer and the second layer is also continuous unlocked and imbricates the first. The primary outcome is the reported number of days with postmenstrual spotting during one menstrual cycle nine months after CS. Secondary outcomes include surgical data, ultrasound evaluation at three months, menstrual pattern, dysmenorrhea, quality of life, and sexual function at nine months. Structured transvaginal ultrasound (TVUS) evaluation is performed to assess the uterine scar and if necessary saline infusion sonohysterography (SIS) or gel instillation sonohysterography (GIS) will be added to the examination. Women and ultrasound examiners will be blinded for allocation. Reproductive outcomes at three years follow-up including fertility, mode of delivery and complications in subsequent deliveries will be studied as well. Analyses will be performed by intention to treat. 2290 women have to be randomised to show a reduction of 15% in the mean number of spotting days. Additionally, a cost-effectiveness analysis will be performed from a societal perspective.

**Discussion:**

This RCT will provide insight in the outcomes of single- compared to double-layer closure technique after CS, including postmenstrual spotting and subfertility in relation to niche development measured by ultrasound.

**Trial registration:**

Dutch Trial Register (NTR5480). Registered 29 October 2015.

**Electronic supplementary material:**

The online version of this article (10.1186/s12884-019-2221-y) contains supplementary material, which is available to authorized users.

## Background

Caesarean section (CS) rates have increased from 14.5 to 27.2% in the last two decades in the Western world. [1] In 2016, 26.664 CSs were performed in the Netherlands, being 16.0% of the total number of deliveries. [2] The increasing CS rate has stimulated an interest in the potential long-term morbidity of a CS scar, such as uterine rupture or malplacentation. [3–7] Other less severe, but more prevalent long-term symptoms are gynaecological symptoms and subfertility.

Only recently, gynaecological symptoms such as painful menstruations and postmenstrual spotting have been associated with CSs. [8–10] These symptoms are considered to be related to a niche, defined as *“an indentation at the site of the caesarean scar with a depth of at least 2 mm”*, visible on transvaginal ultrasound (TVUS). [11] Two cohort studies reported a strong association between postmenstrual spotting and a niche: odds ratio (OR) 3.1; 95% confidence interval (CI) 1.5–6.3 [8] and OR 5.5; 95% CI 1.1–26.5. [10] In these studies, a niche was observed in 50 to 60% of the women after a CS, using transvaginal ultrasound. [8, 10] Spotting was correlated to niche volume and inversely correlated to the residual myometrium thickness (RMT). [8, 10]

In addition to the gynaecological symptoms, a niche may influence fertility. A recent meta-analysis reported that a CS on average reduced the probability of subsequent pregnancy with 9% (relative risk (RR) 0.91; 95% CI 0.87–0.95) in comparison to a vaginal delivery. [12] None of the included studies in this meta-analysis evaluated the relation between subsequent fertility and the presence of a niche. One of the hypotheses is that intra-uterine fluid or cervical mucus or blood accumulation in the niche are expected to hamper the penetration of sperm cells or impair embryo implantation. [13] Long-term follow-up will facilitate the evaluation of the association between uterine closure, niche development, accumulation of intra-uterine fluid and subfertility.

In the last years, various therapies have been developed and implemented to treat niche related symptoms such as menstrual disorders. [14–18] Effectiveness of both hysteroscopic [19] and laparoscopic niche resection [15] have recently been published. Because both niche related symptoms and applied therapies lead to increases in medical consultations and costs, it seems to be more efficient to prevent niche development in the first place. Uterine closure technique of the CS scar has been proposed as an independent factor for niche development. [9] However, large randomised trials evaluating the effect of uterine closuring techniques on postmenstrual spotting or other gynaecological or reproductive outcomes in relation to niche development and thin residual myometrium are lacking, as well as cost-effectiveness evaluations.

In order to shorten surgery time and in the absence of significant differences in short-term outcomes [20, 21], most Dutch gynaecologists (92%) have replaced double-layer by single-layer closure after a CS, using multifilament continuous unlocked sutures. Given the higher risk on myometrium loss and thus development of a thinner residual myometrium after single-layer closure [5, 22], we hypothesise that this method introduces a higher risk on postmenstrual spotting and possibly subfertility after a CS and that it can be prevented by applying double-layer unlocked closure.

Double-layer unlocked closure is considered safe, without a clinically relevant higher risk on short-term outcomes. [5, 23, 24]. Moreover, it results in a thicker residual myometrium, especially when unlocked sutures are applied. [5, 22, 24] Dysmenorrhea was reported more frequently after single-layer closure, but this was only studied in two RCTs and not always related to ultrasound findings such as myometrial thickness or niche presence. [24] Prevalence of uterine rupture seems to be similar after single- versus double-layer closure [5, 22, 24], but has neither been related to ultrasound findings and since it has a very low incidence, statistically significant differences are difficult to find. Since long-term outcomes such as gynaecological symptoms, fertility outcomes and results of subsequent pregnancies are studied infrequently, additional evidence is needed before a preference for either technique can be indicated.

## Objective

Our primary objective is to determine the effectiveness of unlocked double-layer uterine closure compared to unlocked single-layer uterine closure in the prevention of niche related gynaecological symptoms nine months after a first CS. Secondary objectives are to assess niche prevalence measured by ultrasound at three months follow-up and to study both reproductive outcomes related to a subsequent pregnancy and gynaecological symptoms at three years follow-up. Additionally we aim to study the cost-effectiveness alongside the trial.

## Methods/design

### Design

This multicentre randomised controlled superiority trial will be performed in the Netherlands, in hospitals that collaborate within the Dutch Consortium for Healthcare Evaluation and Research in Obstetrics and Gynaecology (NVOG Consortium 2.0, www.zorgevaluatienederland.nl). Centres that participate are district, teaching or university hospitals in the Netherlands. A list of study sites is available in Additional file 1.

### Participants and eligibility criteria

All women who undergo a first CS, planned or unplanned, will be asked to participate in the study. Other inclusion criteria are: sufficient command of the Dutch or English language, age ≥ 18 years and written informed consent. To prevent confounding effects on niche development during the study, we will exclude women with a previous CS. Other exclusion criteria are: inadequate possibility for counselling (e.g. indication for emergency CS without being informed about the study previously, women in severe pain without adequate therapy), previous major uterine surgery (e.g. laparoscopic or laparotomic fibroid resection, septum resection), women with known causes of menstrual disorders (e.g. cervical dysplasia, communicating hydrosalpinx, uterine anomaly or endocrine disorders disturbing ovulation), placenta in- or percreta during the current pregnancy or ≥ three foetuses during the current pregnancy.

### Recruitment and randomisation

Eligible women will be asked by a gynaecologist, resident, clinical midwife or research nurse to participate in the trial when they undergo a planned CS. Eligible women who are planned to undergo a vaginal delivery will also be informed about this study during pregnancy in case they need an unplanned CS. Furthermore, women during induced labour and women receiving adequate therapy for pain during labour, will be asked to participate in case a CS is needed during labour for any indication.

When the decision of a CS is made and all selection criteria are met, women will be randomly allocated to single-layer (control group) or double-layer (intervention group) closure (1:1) (see Fig. 1). Randomisation will be performed using a web-based application ALEA 2.2 which displays a computer-generated random number, managed by the Clinical Research Unit of the Amsterdam UMC - location AMC. We will use a permuted block-design, stratified for recruiting centres and for planned or unplanned CS. All women that decline to participate will be registered anonymously in order to record the number and reason for refusal. Subjects who withdraw from this study will not be replaced. 

Gynaecologists, residents, clinical midwives or research nurses enrol participants and assign them to the intervention. The CS will be performed by either a gynaecologist, a resident supervised by a gynaecologist or by a resident that is authorised to perform CSs without supervision. Participants and sonographers will be blinded for the closure technique. If operative reintervention after CS is needed and the gynaecologist that performs the reintervention needs to know the closure technique that the participant was assigned to, unblinding is possible through the logistic trial coordinator. We expect this situation to occur very infrequently.

### Intervention (double-layer closure)

In both study arms, women will undergo a CS following a standard way with respect to mode of uterotomy, correct approximations of the cutting edges and non-closure of the peritoneum. In the intervention arm, double-layer closure of the uterus will be performed using unlocked multifilament continuous running sutures for both layers and the endometrial layer will be included in the first layer (see Fig. 2). The second layer is a continuous running suture that imbricates the first layer. Since this is not the standard method for uterine closure in the Netherlands, a short online instruction film will be shown to all participating centres and surgeons prior to participation (see Additional file 2). Surgical outcomes will be registered after the procedure in the electronic case report form (eCRF).

**Fig. 1 Fig1:**
[figure not shown]
Flowchart of the 2Close study. * = baseline questions, EQ-5D-5L. ** = symptom questionnaire, EQ-5D-5L, SF36, PROMIS SF8a, iMCQ, iPCQ. *** = symptom questionnaire, FSFI, EQ-5D-5L, SF36, iMCQ, iPCQ. **** = symptom questionnaire, fertility questionnaire, FSFI, EQ-5D-5L, SF36, PROMIS SF8a

### Control group (single-layer closure)

The control group will receive usual closure technique of the uterus: a single-layer closure using unlocked continuous running multifilament sutures. The currently available evidence is inconclusive with respect to endometrial saving technique or not. Therefore, we decided that in our study surgeons are free to choose to close either full thickness (including the endometrium) or split thickness (excluding the endometrium) in the control group. The applied method, including endometrial saving technique or not, will be registered.

### Niche evaluation

The care after CS will be according to the normal local protocol with the regular outpatient visit that is normally executed six weeks after the CS. This routine visit may be postponed to three months after the CS to enable an ultrasound evaluation to identify the existence of a niche, but participating centres may decide whether they want visits at six weeks (routine follow-up) and at three months (ultrasound follow-up) or only one visit after three months combining the regular control and the ultrasound follow-up. The ultrasound evaluation is standardised as proposed by Jordans et al. [11] (see Fig. 3). Based on this standardisation, we created an obligatory e-learning for all ultrasound performers to let all ultrasounds be performed in a uniform manner. To increase consistency and to improve the learning curve, we will evaluate a sample of ultrasounds in each centre based on recorded pictures and provide feedback to the examiners. Since it is known that a niche can be missed during TVUS only [8, 10, 25] we will additionally perform a saline infusion sonohysterography (SIS) or gel installation sonography (GIS) in case no niche is observed during the normal TVUS or if the ultrasound is inconclusive. It would be optimal to have a contrast enhanced ultrasound in all women when the uterine cavity or niche are not naturally filled with fluid, but we have chosen for this approach to prevent unnecessary burden for the participants and to reduce costs.

**Fig. 2 Fig2:**
[figure not shown]
Double-layer uterine closure technique. **a**. Step 1: lateral suture; **b**. Step 2: lateral suture on the other side; **c**. Step 3: First layer: full thickness, continuous, including large part of myometrium, including the endometrial layer; **d**. Step 4: End of this first layer; **e**. Step 5: Second layer: superficial continuous layer of serosal tissue, imbricating the first layer; **f**. Step 6: First and second layer should be closely connected

### Outcome measures

#### Primary outcome measure

The primary outcome is the number of days of postmenstrual spotting during one cycle at nine months after CS. We defined postmenstrual spotting as brownish discharge for more than two days at the end of the menstruation, with a total duration (menstruation and spotting) of more than seven days, or intermenstrual blood loss that starts after the end of the menstruation. [8] The number of days of postmenstrual spotting will be counted as follows: days with brownish discharge (> two days) when the total duration of menstruation and spotting exceeds seven days + number of days with intermenstrual blood loss. Amenorrhoeic women, due to lactation, medication or other diseases, will not be evaluable for the primary outcome and will be left out of this analysis.

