#### Secondary outcome measures at short-term

Perioperative outcomes including blood loss, operative time, additional haemostatic sutures and complications.Menstruation characteristics, dysmenorrhea (visual analogue scale (VAS)), Quality of Life (QOL) using Short-Form-36 [26] and EQ-5D-5L [27, 28], societal reintegration (PROMIS Short-Form-8a [29]), sexual function using the Female Sexual Function Index (FSFI [30]), applied medical and/or surgical therapy because of gynaecological symptoms, all obtained through digital questionnaires, will be assessed at three and nine months follow-up.Ultrasound evaluation will be performed at three months follow-up using TVUS, in which RMT, adjacent myometrium thickness (AMT), presence of a niche (depth of ≥2mm), length, depth and width of the niche, presence of large niches (RMT < 50% of AMT, RMT <3mm) and niche volume will be measured.

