### Statistical issues

#### Sample size calculation

We use a superiority design since we expect double-layer closure to be favourable. Literature for making reliable estimations on postmenstrual spotting in relation to niches is scarce. We have used baseline data from the HysNiche [19] and LapNiche [15] study. We estimate the mean number of spotting days to be 3.5 days/month in the total group. We consider a 15% reduction in the mean number of spotting days clinically relevant, which is 0.5 day/month reduction. Assuming a standard deviation (SD) of 3.4 and a two-sided significance level of 5%, a total of 1488 women need to be included to achieve a power of 80%. Increasing the sample size to take into account 35% of women unevaluable (due to drop-out, non-response or amenorrhoea) for the primary outcome, 2290 women need to be included.

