#### Data-analysis

Data-analysis will be performed according to the intention to treat principle and additional per protocol analyses will be performed. A test will be considered statistically significant when the two-sided test shows a *p*-value < 0.05. Baseline characteristics will be presented using percentages, means with SD and 95% CI or medians with interquartile ranges (IQR), where appropriate.

The primary outcome, number of days of postmenstrual spotting, will be presented for both groups as mean with SD or median with IQR, and presented in a Box-Whisker graph to show the distribution. Differences in primary outcome between the groups will be tested using the independent t-test in case of normal distribution (possible after transformation of the outcome) or Mann-Whitney U test. An adjusted analysis will be performed using linear regression analysis in which we adjust for factors on which randomisation was stratified and for baseline factors on which relevant differences are observed despite randomisation.

Dichotomous secondary outcomes will be presented as percentages and RR with corresponding 95% CI. *P*-values will be calculated using the chi-square test or, if the expected count for at least one cell is below 5, using the Fisher exact test. Normally distributed continuous variables will be presented as means with SD, and differences between the groups will be calculated with an independent t-test. Non-normally distributed continuous variables will be presented as medians with IQR and differences between the groups will be calculated with Mann-Whitney U test. The questionnaires will be analysed using the appropriate algorithms and usual presentation methods (FSFI, EQ-5D-5L, SF36, PROMIS SF8a, iMCQ, iPCQ).

Comparison of primary outcome between women receiving single- and double-layer closure will be done as secondary analyses within each of the following subgroups separately:Planned (without labour) or unplanned (in labour) CSEmergency CS or notPreterm (< 37 weeks gestational age) or term (≥ 37 week gestational age) CSPresence (> 3cm) or absence (≤ 3cm) of dilatationPlacenta praevia or notPresence or absence of specific maternal morbidity (e.g. diabetes, pre-eclampsia, haemolysis/elevated liver enzymes/low platelet count (HELLP) syndrome, immunodeficient women)Singleton versus twin pregnancyNatural cycle or hormonally induced withdrawal bleeding

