#### Economic evaluation

The economic evaluation will be performed alongside the RCT from a societal perspective. Both a cost-effectiveness and cost-utility analysis will be performed with a time horizon of nine months to relate the difference in societal and healthcare costs between double-layer and single-layer unlocked uterine closure during a CS to the difference in clinical effects. Healthcare costs include costs of primary and secondary care, complementary care and home care. Costs in other sectors include presence and absence from paid and unpaid work. The friction cost approach will be used to estimate indirect costs. For the valuation of health care utilization standard prices published in the Dutch Costing guidelines will be used. [34] Medication use will be valued using prices of the Royal Dutch Society for Pharmacy.

Societal costs will be related to the following effect measures in the economic evaluation: days with postmenstrual spotting and quality-adjusted life-years (QALYs) based on the Dutch tariff for the EuroQol (EQ-5D-5L). [27, 28, 35]

We hypothesise that double-layer uterine closure will reduce postmenstrual spotting and related consultations for gynaecological or fertility related problems and applied therapies, and as a consequence that it will be cost-effective in comparison with single-layer uterine closure.

The analysis will be done according to the intention to treat principle. Missing costs and effect data will be imputed using multiple imputation. Incremental cost-effectiveness ratios (ICERs) will be calculated by dividing the difference in mean total costs between the treatment groups by the difference in mean effects. Bootstrapping with 5000 replications will be used to estimate 95% CI around cost differences and the uncertainty surrounding the ICERs. Uncertainty surrounding the ICERs will be graphically presented on cost-effectiveness planes. Cost-effectiveness acceptability curves showing the probability that double-layer uterine closure is cost-effective in comparison with single-layer uterine closure for a range of different ceiling ratios will also be estimated. Adjustment for confounders and effect modifiers will be done if necessary. [36]

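### The primary analysis leaves out every woman with medication-induced amenorrhoea, including any whose bleeding was suppressed to treat spotting, so the estimated difference may be biased, most likely towards zero

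*Protocol article*

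**What the plan says.** Primary outcome measure: "Amenorrhoeic women, due to lactation, medication or other diseases, will not be evaluable for the primary outcome and will be left out". Medication is named without regard to why it was taken.

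Data-analysis: "Data-analysis will be performed according to the intention to treat principle and additional per protocol analyses will be performed". The Methods part of the Abstract also describes the analyses as by intention to treat.

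Sample size calculation: the number to be randomised is inflated for "35% of women unevaluable (due to drop-out, non-response or amenorrhoea"), three causes in one figure.

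Three further statements bear on the rule:

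- The Background says that "various therapies have been developed and implemented to treat niche related symptoms such as menstrual disorders".
- Secondary outcome measures at short-term includes "applied medical and/or surgical therapy because of gynaecological symptoms", collected by questionnaire at three and nine months.
- The Economic evaluation section says: "We hypothesise that double-layer uterine closure will reduce postmenstrual spotting and related consultations for gynaecological or fertility related problems and applied therapies".

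The Data-analysis section also lists a subgroup comparison by natural cycle or hormonally induced withdrawal bleeding. Hormone users who still bleed therefore stay in. Complete absence of bleeding is what removes a woman.

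**The concern.** Amenorrhoea at nine months is a state reached after allocation. Lactational amenorrhoea is plausibly unrelated to how the uterus was closed. Amenorrhoea from medication is not safely unrelated, because one reason to take such medication is the symptom that the trial measures. A woman treated for spotting who no longer bleeds at nine months would drop out of the comparison because of her outcome.

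The protocol's own hypothesis makes this a possible difference between the arms. If single-layer closure produces more spotting and more therapy for it, more of the badly affected women leave the single-layer mean than leave the double-layer mean, and the analysed difference understates the real one. Inflating the sample size replaces lost numbers. It does not correct selection that differs by arm.

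**Working it through.** **1. The plan's own figures.** Inputs from the Sample size calculation: difference 0.5 day, SD 3.4, two-sided 5%, power 80%, 35% unevaluable.

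- Per arm: n = 2(1.960 + 0.842)² × 3.4² / 0.5² ≈ 726, so 1452 in total. The plan states 1488; the computed figure is 2.4% lower, which is close enough.
- Inflation: 1488 / 0.65 = 2289.2, rounded up to 2290, as stated.
- Women allowed to be outside the primary analysis: 2290 − 1488 = 802. This pools drop-out, non-response and amenorrhoea of every cause. The part due to medication, or to medication for spotting, cannot be derived.

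**2. What drives the bias.** Take true means of 3.5 and 3.0 days (the plan's mean and difference, assigned to the arms by assumption). Let a share q of an arm be removed whose mean would have been m days. The analysed arm mean is (true mean − q·m) / (1 − q). The values of q and m below are assumptions.

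| Removed, single / double | m | Single | Double | Difference |
|---|---|---|---|---|
| 5% / 5% | 7 | 3.15/0.95 = 3.316 | 2.65/0.95 = 2.789 | 0.53 |
| 5% / 2.5% | 7 | 3.15/0.95 = 3.316 | 2.825/0.975 = 2.897 | 0.42 |
| 5% / 2.5% | 10 | 3.00/0.95 = 3.158 | 2.75/0.975 = 2.821 | 0.34 |

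Equal removal does not shrink the difference. The shrinkage comes from imbalance between the arms.

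**3. A model in which the imbalance follows from the effect itself.** All inputs are assumptions. A proportion p of women spot. Spotters have gamma-distributed days with mean 6.8 and SD 3.0. Control p is 0.515 or 0.40. Double-layer p is lower by 0.5/6.8 = 0.0735 (so 0.4415 or 0.3265), which makes the true difference 0.5 day. Women above a common threshold, set at the heaviest fraction f of control spotters, are removed. With A the mean of spotting days after days above the threshold are set to zero, the analysed mean is p·A / (1 − p·f).

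| f | A | Difference, control p 0.515 | Difference, control p 0.40 | Attenuation |
|---|---|---|---|---|
| 2% | 6.476 | 3.370 − 2.885 = 0.485 | 2.611 − 2.128 = 0.483 | about 3% |
| 5% | 6.081 | 3.214 − 2.745 = 0.469 | 2.482 − 2.018 = 0.464 | 6-7% |
| 10% | 5.505 | 0.446 | 0.436 | 11-13% |
| 30% | 3.664 | 0.367 | 0.339 | 27-32% |

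The 30% row removes 0.3 × 0.40 = 12% to 0.3 × 0.515 = 15% of all control women as medically suppressed by nine months.

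**4. How well the model fits the plan.** Its control SD is √[p(3.0² + 6.8²) − (6.8p)²] = 4.02 at p = 0.515 and 3.83 at p = 0.40, against the plan's 3.4. At p = 0.40 the control mean is 2.72 days, although the plan puts the overall mean at 3.5. Removing the heaviest spotters also lowers the SD. At 744 per arm before removal, power for control p 0.515 is about 0.68-0.69 with no removal, 0.70 at f = 10% and 0.67 at f = 30%. For p 0.40 it is 0.73, 0.74 and 0.69.

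**The case against.** The mechanism is inferred. Nothing in the protocol says that medication for spotting makes women amenorrhoeic in this trial, or how often. Medication is listed beside lactation and other diseases, which fits contraception as well as treatment. Participants are blinded to closure technique and are not told whether a niche is present, so only symptoms can drive treatment. Women with withdrawal bleeding stay in. All of this stands, and it limits the likely size. It does not remove the route, because symptoms are exactly what the protocol expects closure to change.

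The outcome is defined relative to a menstruation, so a woman without a cycle has no count. That is a fair reason to set aside lactational amenorrhoea. It is a weaker reason for treating suppression of the symptom by therapy as the same kind of non-evaluability.

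The intention-to-treat wording can be read as analysis by allocated arm, in contrast to per protocol, and the exclusion is disclosed. That stands, so this part is a matter of reconciling wording. Detailed sensitivity analyses may also sit in an analysis plan that is not shown. The exclusion rule, however, is fixed in this article.

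Two stronger readings are tempting. One is that about a third of the benefit, or much of the power, could be lost. The documents do not support this: the 27-32% figures need 12-15% of all control women to be suppressed, and power in that model barely moves. The lower power from the 5% versus 2.5% scenario (66% to 48%, against 81%) rests on an assumed two-to-one removal rate and an SD held at 3.4. The other is that 35% of women are removed by this rule. That figure pools several causes, and the relevant share is unknown.

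**Conclusion.** The point holds as a flaw in a stated rule, with modest and unquantified consequences. The exclusion covers medication-induced amenorrhoea whatever the reason for the medication, while the protocol expects allocation to change the use of therapy for these symptoms. The primary comparison can therefore be biased, most likely towards zero.

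The attenuation may be small: about 3-7% of a 0.5-day difference if the heaviest 2-5% of spotters are lost. This rests on the assumed model, on a common removal threshold, and on the benefit coming wholly from fewer women spotting. If closure instead shortened spotting, a common threshold would remove more unequal shares and the attenuation would be larger. The effect is mainly on the estimate; in this model the power of the primary test is little affected.

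**What to change.** - Classify amenorrhoea at nine months by cause, using the data on therapy for gynaecological symptoms that are already collected.
- Restrict the exclusion to causes unrelated to bleeding symptoms.
- Keep women whose bleeding is suppressed by therapy for gynaecological symptoms and give them a prespecified unfavourable score, for example worst rank, at least in a prespecified sensitivity analysis. Carrying forward a three-month value is not a reliable substitute: the exact menstrual and spotting chart is stated only for nine months, and some women may still be amenorrhoeic from lactation at three months.
- Add a sensitivity analysis of all nine-month responders with other amenorrhoea scored as 0 spotting days. This does not cover drop-outs and non-responders and should not be presented as all randomised women.
- Report amenorrhoea by cause and by arm.
- Describe the primary analysis as evaluable women analysed by allocated arm, and reconcile the Primary outcome measure section with the intention-to-treat wording in the Abstract and the Data-analysis section.

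The cost is an assigned score for what is probably a small group and slightly more analysis work. No additional questionnaire data are needed if the therapy items show which women were treated for gynaecological symptoms.
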